#### Diagnostic and Screening Assessments

At screening, standard demographic information will be collected from all participants (e.g., gender, race, ethnicity, etc.). Contact information will be obtained and updated monthly and additionally as needed. DSM-IV-TR alcohol and substance abuse and dependence will be assessed with the substance use modules of the World Health Organization (WHO) Composite International Diagnostic Interview (CIDI) (Version 2.1)[55,56]. Additional DSM-IV Axis I diagnostic information will be obtained using the MINI International Neuropsychiatric Interview (MINI)[57].

#### Medical Evaluation

Medical history will be obtained using a self-report medical history form designed to collect information about history and/or treatment of medical conditions, such as heart disease, high blood pressure, diabetes, and cancer. The form also assesses allergies, past surgeries, tobacco and alcohol use, family history of medical conditions, medical symptoms over the past 30 days, and prior and concomitant medications. Additionally, participants will complete the Self-Administered Comorbidity Questionnaire (SCQ)[58] and the Physical Activity Readiness Questionnaire (PAR-Q)[59]. Medical personnel will conduct a medical history and physical exam, and laboratory tests (chemistry, hematology, lipid profile, and urinalysis) will be obtained as part of the medical screening process.

Maximal exercise testing will be conducted during the screening process to examine cardiorespiratory responses in order to rule out ischemic response to exercise (with its implications of cardiovascular disease), to identify participants for whom exercise might be hazardous, and to provide data for the exercise prescription. The test will be repeated at the end of the 12-week acute phase (or during an early termination visit). A trained technician will process the test data and a report will be generated that contains the following information: 1) participant's symptoms before, during, and after testing; 2) maximal heart rate achieved and percent of predicted maximal heart rate achieved; 3) time on treadmill and estimated maximal metabolic equivalent (METS) achieved; and 4) ECG interpretation. A designated medical staff member will be responsible for reviewing the participant's medical history and evaluating results from the medical exam, maximal testing, and lab results to determine whether or not the participant is medically cleared to exercise.

Eligible participants complete a comprehensive baseline assessment. Since there are numerous baseline assessments, these may be distributed over more than one day if necessary. The frequency and type of ongoing assessments are equivalent in both groups, with the exception of blood pressure and heart rate obtained for exercise participants prior to every supervised exercise session. Descriptions of ongoing study assessments are described by category below (as well as in Table 2).

#### Substance Use and Treatment Assessments

The Timeline Followback [48,49] and Substance Use Diary (SUD) will be used to acquire information on alcohol and drug use, including cocaine and other stimulants. The TLFB is a semi-structured interview that uses a calendar to prompt participants to provide retrospective estimates of their daily drug use over a specified period of time that can vary up to 12 months before the interview date. The measure provides prompts to facilitate accurate recollection of use behavior. The SUD, a pocket calendar given to participants at the beginning of the study to prospectively record substance use, will assist with accurate recall when completing the TLFB at each study visit.

Qualitative urine drug screens (UDS) will be conducted at baseline, three times a week in the first 12 weeks, and once a week in the subsequent 6 months. The screen will test for the following substances: marijuana, cocaine, opiates, amphetamine, methamphetamine, benzodiazepines, barbiturates, methadone, methylenedioxymethamphetamine (MDMA, Ecstasy), and oxycodone. UDSs will also be used to corroborate information on the TLFB.

The Addiction Severity Index-Lite (ASI-Lite) will be administered by research staff to examine multiple domains that are commonly affected by substance use, including medical, employment/self-support, alcohol/drug use, legal status, family/social, and psychiatric status [60]. Stimulant craving (cocaine, methamphetamine, and other stimulants) will be assessed using the Stimulant Craving Questionnaire-Brief (STCQ-Brief; adapted from Sussner et al. [61] and derived from the 10-item Cocaine Craving Questionnaire-Brief and the original 46-item Cocaine Craving Questionnaire-Now [62]). Signs and symptoms of stimulant (cocaine, methamphetamine, and other stimulants) abstinence will be evaluated using the Stimulant Selective Severity Assessment (SSSA; adapted from Kampman et al. [63]). Baseline nicotine dependence will be evaluated using the Fagerstrom Test for Nicotine Dependence (FTND)[64,65] and number of cigarettes smoked per day will be captured on the TLFB.

#### Mood and Functional Measures

Symptoms of depression will be measured by the Quick Inventory of Depressive Symptomatology - Clinician Rated version (16-item)[66-70], and the Snaith-Hamilton Pleasure Scale (SHAPS)[71] will be used to measure anhedonia. Suicidality and related symptoms will be evaluated throughout the study using the Concise Health Risk Tracking - Self-Report (CHRT-SR), and the Concise Associated Symptoms Tracking - Self-Report (CAST-SR).

Psychosocial assessments will include the Quality of Life Enjoyment and Satisfaction Questionnaire Short Form (Q-LES-Q-SF [72]), the Short-Form Health Survey (SF-36 [73,74]), and the Pain Frequency, Intensity and Burden Scale (P-FIBS). Assessments of cognitive function will include the Stroop Color and Word Test [75,76], a measure of attention response inhibition, and the MGH Cognitive and Physical Functioning Questionnaire (CPFQ [77]), a measure of subjective cognitive function. The Wechsler Test of Adult Reading (WTAR [78]) will be administered at baseline to assess premorbid intelligence.

#### Fitness and Physiological Measures

Physiological measures include height, weight, body mass index (BMI), and waist circumference. For those participants in the exercise intervention, resting heart rate and blood pressure will be obtained prior to each exercise session using the Exercise Readiness Form in order to evaluate safety to exercise. Resting heart rate and blood pressure will be obtained for all participants during the maximal exercise test. The maximal exercise will be repeated at week 13 to assess change in fitness.

#### Retention

The Treatment Participation Questionnaire (TPQ), a five-item self-report that assesses the participant's likelihood of remaining in treatment for substance abuse and continuing to attend study visits, will be administered at baseline and then weekly thereafter. Since this study is designed as an intent-to-treat study, subjects will be encouraged to complete assessments regardless of their status in their treatment programs or their engagement in the study intervention.

#### Analytic Methods

The primary analysis will compare the primary outcome between the two treatments taking into account possible variability in the overall level of abstinence between sites. More specifically, we use a mixed normal model with a fixed treatment effect and random terms for site and error. The model considers treatment effect to be the same in each site. P-value less than 0.05 will be considered statistically significant. The assumed treatment effect *μ_VIHD_*-*μ_HEC _*is 0.15. The error standard deviation *σ *is considered to be in the range between 0.40 and 0.45, and abstinence status within participant is assumed to be correlated across days. The primary endpoint will be analyzed on an intent-to-treat basis, meaning that participants' data will be analyzed according to the group they were randomized to, regardless of the subsequent sequence of events (e.g., noncompliance to the intervention).

Even though the overall level of outcome may differ across sites (i.e. *σ_site _*> 0), the primary analysis removes this variation by adjusting for site in the model. Hence, initial sample size computations are based on value of error standard deviation *σ *and the sample size estimates are based on a two sample t-test formula. A treatment effect that varies across sites may contribute additional variation and simulations with primary analysis performed for each simulation were used to investigate this possibility. Based on these simulations, and as an additional precaution, we increased initial sample size by 10% to attempt to take into consideration potential treatment effect variability. Based on these considerations, we proposed the trial to enroll 330 participants. Clearly, the proposed sample size depends on accurate estimation of variability *σ*. We propose to reassess this variability midway through the study, i.e., after approximately 165 participants have enrolled and completed the acute phase of the trial, and may readjust needed sample size if the variance assumption proves incorrect.

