Physical Exam/Medical History	Screen	To provide clearance for exercise.

Laboratory Tests	Screen	To provide clearance for exercise.

*Substance Use and Treatment Assessments*		

Timeline Followback (TLFB)* *Primary outcome measure	Screen, 3X/wk for 1^st ^3 months, 1X/wk for next 6 months	To quantify days of substance use for calculation of primary outcome (percent days abstinent). The TLFB has been shown to have high test-retest reliability (ICC values ranging from 0.70 to .94, with all p < 0.001), good convergent and discriminate validity, and acceptable agreement between the TLFB and urine drug screens (Yule's Y of 87 or greater for amphetamines and cocaine)[114].

Urine Drug Screen (UDS)	Baseline, 3X/wk for 1^st ^3 months, 1X/wk for next 6 months	To test for substance use and to inform TLFB.

Stimulant Craving Questionnaire-Brief (STCQ-Brief)	Baseline, weekly	To assess current craving for stimulants. The CCQ-Brief, from which the STCQ-Brief is adapted, has high internal consistency, with Cronbach's alpha ranging from 0.87 [115] to 0.90 [61]. The instrument also has good construct validity and has shown to correlate well with other craving measures [115].

Stimulant Selective Severity Assessment (SSSA)	Baseline, weekly	To assess signs and symptoms of stimulant abstinence. The Cocaine Selective Severity Assessment, from which the SSSA is adapted, has been shown to have good inter-rater reliability (correlation coefficient = 0.92, p < 0.001) and internal consistency (Cronbach's alpha = 0.80).

Addiction Severity Index-Lite (ASI-Lite)	Baseline, weeks 13, 25, 37	To assess common problems associated with drug use. The CTN version is similar to the ASI-Lite-Veterans Administration (ASI-L-VA) and should have similar psychometric characteristics. Specifically, intraclass correlations between the ASI fifth edition (ASI-5) and ASSI-L-VA are 0.79 for alcohol, 0.79 for drug, 0.85 for legal, 0.46 for family/social, and 0.53 for psychiatric [116].

Fagerstrom Test for Nicotine Dependence (FTND)	Baseline	To assess dependence on nicotine. The FTND has shown acceptable internal consistency (Cronbach's alpha of 0.61) and correlates significantly with other measures of smoking consumption.

Treatment as Usual (TAU) Tracking Form	Baseline, weekly	To assess the participant's treatment for substance abuse within the past week.

*Measures of Mood, Sleep and Anhedonia*		

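### The stated primary model adjusts for site but not for baseline stimulant use, which is already collected; adding it is a nearly free improvement, not the repair of an error

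*Protocol article*

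**What the plan says.** All references are to the protocol article.

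- **Model.** Analytic Methods states the primary analysis as follows: "we use a mixed normal model with a fixed treatment effect and random terms for site and error". The treatment effect is taken as common to all sites, and site is the only factor adjusted for. The article neither includes baseline substance use nor discusses leaving it out.
- **Significance.** "P-value less than 0.05 will be considered statistically significant". Sidedness is not stated.
- **Sample size.** The assumed difference is 0.15, and the error SD "is considered to be in the range between 0.40 and 0.45". The section says that "the sample size estimates are based on a two sample t-test formula", that "we increased initial sample size by 10% to attempt to take into consideration potential treatment effect variability", and that on this basis "we proposed the trial to enroll 330 participants". It adds that the number depends on σ, which is to be reassessed about midway.
- **Baseline data.** Study Assessments, Table 2, lists the TLFB at screening and then throughout follow-up, with the purpose "To quantify days of substance use for calculation of primary outcome (percent days abstinent". The same table and the Substance Use and Treatment Assessments section place a urine drug screen at baseline.

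**The concern.** A measure of stimulant use before randomisation, taken with the outcome instrument itself, is a usual candidate covariate for a continuous outcome. If it predicts abstinence, leaving it out keeps explainable variation in the error term, and σ is the quantity on which the plan says its sample size depends. The article justifies its site term by saying that it removes variation between sites; the same reasoning applies to variation between participants in earlier use.

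The second matter is chance imbalance. Eligibility requires some stimulant use in the 30 days before admission and admits both abuse and dependence, so severity at entry can differ between participants and, by chance, between arms. The stated model does nothing about that. A covariate added after an imbalance has been seen is open to challenge; one named beforehand is not.

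**Working it through.** **Inputs from Analytic Methods.** Difference δ = 0.15; error SD σ = 0.40 to 0.45; N = 330; significance level 0.05; 10% inflation.

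**Assumptions, because the article does not state them.** Two-sided test; 1:1 allocation (165 per arm); correlation r between baseline use and outcome, within arm and site, from 0 to 0.5.

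**Step 1: reproduce the plan's own figure.** The normal-approximation formula is n per arm = 2(z₀.₉₇₅ + z_power)²σ²/δ². With σ = 0.40 and 90% power:

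n = 2 × (1.960 + 1.282)² × 0.16 / 0.0225 = 149.4, rounded up to 150.

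That is 300 in total, and 300 × 1.10 = 330, an exact match. The 90% power is inferred from this match, not stated. Other inputs come close (σ = 0.425 with 85% power and the t version gives 322). The calculation takes no credit for any baseline covariate.

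**Step 2: effect of a covariate.** Adjustment multiplies the error variance by 1 − r², so σ becomes σ√(1 − r²). The standard error of the difference is σ√(1 − r²) × √(2/165), and the equivalent unadjusted sample size is 330/(1 − r²). For example, at σ = 0.45 and r = 0.3 the residual SD is 0.45 × √0.91 = 0.429, and the standard error falls from 0.0495 to 0.0473.

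**Step 3: power.** Two-sample t-test (noncentral t), 165 per arm, δ = 0.15, two-sided 0.05:

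| r | Variance removed | Equivalent N | Power, SD 0.45 | Power, SD 0.40 |
|---|---|---|---|---|
| 0 | 0% | 330 | 85.5% | 92.5% |
| 0.1 | 1% | 333 | 85.9% | 92.7% |
| 0.2 | 4% | 344 | 86.9% | 93.4% |
| 0.3 | 9% | 363 | 88.6% | 94.5% |
| 0.4 | 16% | 393 | 90.9% | 96.0% |
| 0.5 | 25% | 440 | 93.6% | 97.5% |

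**Reading the table.** At r = 0.1 the gain is under half a power point at either SD. At r = 0.2 it is 1.4 points (SD 0.45) or 0.9 points (SD 0.40). At r = 0.3 it is about 3 or 2 points, and at r = 0.5 about 8 or 5 points. A correlation of about 0.3 is worth 363/330 = 1.10, the same proportion as the 10% added to enrolment.

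**Limit of the calculation.** It treats participant-level error as the only source of variance. Variation of the treatment effect across sites, for which the 10% was added, is not included, and baseline adjustment need not reduce it.

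**The case against.** The strongest reply is that nothing here is wrong. The unadjusted comparison is valid under randomisation, the sample size was computed from an unadjusted SD and so borrows no power from adjustment, and the midway reassessment of σ already guards against a poor variance assumption. All of that stands.

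It can also be said that a design article condenses a fuller plan, and that a covariate list may sit in an analysis plan not shown. That is possible, and it bears on whether the change is still needed. But the article gives the model's terms specifically, so the recommendation addresses a stated analysis rather than an absent detail.

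A reader might infer the stronger claim that precision is definitely being thrown away. The documents do not support it, because they give no value for r and several features could make it low. Every participant is a recent user. The Population section says that stimulant users were chosen to limit heterogeneity in drug use. All start in residential care. The Primary Outcome section notes the short half-life of stimulants, so a baseline urine result may partly reflect days since admission; the screening TLFB is therefore the better candidate. Nor may one assume that the screening TLFB covers the 30 days before admission: that period comes from the eligibility criterion, and the article says only that the TLFB window can vary up to 12 months.

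These points limit the expected gain. None of them makes adjustment harmful.

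**Conclusion.** The point holds as a low-severity efficiency recommendation. The stated model contains treatment and site only, while baseline stimulant use is collected in any case. The plan may forgo some precision and has no protection against chance imbalance in earlier use. It is not invalid, and this point does not show it to be underpowered.

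The omission is clear from the text; the size of the gain is not. It ranges from nothing at r = 0 to about 8 power points at r = 0.5 with SD 0.45, or about 5 points with SD 0.40, and it is small at r of 0.2 or less. These figures rest on assumed 1:1 allocation, a two-sided test, an assumed r and no treatment-by-site variation.

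**What to change.** Before any comparison by arm, amend the primary model to include stimulant-use days from the screening TLFB as a fixed covariate, over whatever look-back window that assessment covers, and state the window. The baseline stimulant urine result may be added as an optional second covariate. Keep the site term, and report the model without baseline covariates as a supportive analysis. If this is adopted, the midway reassessment should use the residual SD from the same adjusted model.

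The cost is a sentence of wording and one or two degrees of freedom out of roughly 330. No new data, visits or participants are needed. If the full analysis plan already specifies this adjustment, no change is required.

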## Rationale for Key Study Design Choices

### Population

For this study, we chose to specifically evaluate individuals with stimulant abuse or dependence. This decision was made in order to reduce heterogeneity of the sample with respect to drug use, since this is an early efficacy trial with a new intervention in a substance using population.

### Setting

This study is designed to start while participants are in a residential setting and continues as participants transition into outpatient and other community care. Starting treatment in the residential setting was chosen to maximize the availability of participants to be present for the initial evaluation and training of the exercise intervention. Given the dose and intensity of exercise selected for this study, it is critical that participants be consistent in attending supervised sessions, particularly as they are first learning how to implement the exercise protocol, how to use all related equipment, and how to collect and record all exercise-related data. A transition to outpatient care is a typical occurrence in the treatment of substance use disorders. This study is designed to evaluate participants as they transition to the next phase of care. While the decision to begin in a residential setting could result in somewhat less generalizability of findings, since this is an early efficacy study, we determined that it was more important to ensure that our study population was present to receive sufficient training and supervision in the exercise intervention and to maximize adherence during this time.

### Study Duration

The total duration of participation in STRIDE is 9 months. A 6-month duration for the continuation phase was selected because we would like to see if there is a sustained response to the exercise intervention. In most chronic diseases, longer-term outcomes are best seen in the 6 months following acute phase intervention.

### Exercise Intervention

One of the major hurdles in successfully conducting exercise trials has been the inconsistency of type, dose, and intensity of exercise achieved. We elected to define exercise type, dose and intensity in this study to minimize variability and to achieve pre-specified targets for both dose and intensity.

#### Type

We selected the use of aerobic exercise in this trial. While there is some evidence that other types of exercise (e.g., weight training) may be beneficial to individuals with other disorders, such as depression, the preponderance of existing evidence supports the use of aerobic exercise. Furthermore, aerobic exercise has been used in previous interventions involving substance abuse disorders [7-11,18].

#### Dose

A 12 KKW dose of exercise was selected for this study for the following reasons: 1) it is consistent with U.S. 2008 Physical Activity Guidelines http://www.health.gov/paguidelines, as well as prior recommendations from groups such as the Centers for Disease Control and Prevention and ACSM [79-83], the NIH Consensus panel [45,79,80,82-86], and the U.S. Surgeon General (U.S. Department of Health and Human Services [87]); 2) it has been used in previous studies involving physical activity interventions in smokers [7,9], and in other disorders such as depression [54,88-91], it is consistent with doses associated with biological changes that we hypothesize will impact stimulant use such as alterations of the serotonergic [92-94] and endocannabinoid systems [95], attenuated stress responses [96,97], and increases in release of BDNF [98].

#### Intensity

An intensity range of 70-85% of an individual's HR_max _was selected for this study. This intensity is above the suggested minimum intensity of 50% of HR_max _and within the currently recommended training intensity guidelines for producing physiological adaptations and benefits [51]. Although higher exercise intensities may produce greater changes in outcomes at a constant dose, for this efficacy trial we want to be certain that we are well within standard exercising ranges for both dose and intensity. By selecting a range of 70-85% of HR_max_, we have allowed for some exercising flexibility to increase comfort, while ensuring that all participants are exercising above the minimum recommended threshold.

Alternatively, we could have allowed participants to select their own exercise intensity (i.e., self-selected intensity based on rating of perceived exertion) as long as they achieved the target dose. While this approach would allow significantly greater flexibility for participants, it would likely lead to greater variations in exercise intensity. Another alternative would be to have a fixed exercise intensity (i.e., 80% HR_max_) to maximize the standardization of the exercise intervention. However, a fixed intensity would allow little flexibility for participants to find a comfortable exercise level and may, therefore, result in poor adherence and increased drop-outs.

